#### SCED Procedure

We created a working version based on the Risk of Bias in N-of-1 Trials (RoBiNT) scale, a critical evaluation tool to evaluate the methodological quality of intervention studies using single-case methodology (Tate et al., 2013). We outlined the procedure for routine clinical care and research projects that could use the infrastructure of the single-case clinic in the future. For routine clinical care, we plan to use a replicated ABCDE design in which EMA data is collected after the initial appointment (phase A: baseline), during up to five diagnostic sessions (phase B: diagnostic), and during the first treatment sessions (phase C: intervention). Whenever psychotherapists alter their treatment focus or change their therapeutic strategies, they can initiate a new intervention phase (phase C’, phase C’’, etc.). This allows them to directly continuously evaluate their respective therapeutic approach. Furthermore, ESM data will be collected after treatment has ended (phase D: posttreatment) and at 6-months follow-up (phase E: follow-up). Further details can be found in Table 1.

**Table 1 Tab1:** Working version for the implementation of the single-case clinic based on the RoBiNT Scale (Study 2)

Item	RoBINT Scale	Suggestions for the implementation into routine clinical care	Possibilities for future research projects
*Internal validity subscale*			
1	Design	Replicated ABCDE Design A: baseline phase B: diagnostic phase C: intervention phase (C’, C’’, etc.) D: posttreatment phase E: follow-up phase	Replicated *randomized* designs Multiple baseline designs (concurrent and non-concurrent)
2	Randomization	No randomization due to practice-oriented focus	Randomization of treatment start per patient; randomization of treatment components (and their order)
3	Sampling behavior (all phases)	Baseline, diagnostic, posttreatment, and follow-up phase: 14 surveys per phase Intervention phase: open end	At least 5 data points per phase; patients with less than 3 data points per phase should be excluded from any statistical analysis
4	Blinding patient/psychotherapist	Blinding not possible and unethical	Blinding options are restricted in psychological treatments; in the case that interventions are compared against each other, neither patients, psychotherapists, nor supervisors should be informed about the research hypothesis

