#### ESM Protocol

We followed systematic guidelines to consider different arguments when making methodological decisions (Janssens et al., 2018). A decision matrix was created that organizes different arguments along methodological questions (Supplemental Material, S3 Decision matrix for methodological questions, https://osf.io/54ewu). Arguments include the nature of the variable of interest, reliability and feasibility issues, as well as statistical requirements. Open methodological questions include study duration, measurement frequency, number of items, sampling scheme, instruction of items, and delay allowed to respond. The matrix was filled with typical practices or recommendations for ESM studies found in the literature (Eisele et al., 2020; Janssens et al., 2018; Wrzus & Neubauer, 2023). Based on the matrix, the research team formulated methodical suggestions for the SCED infrastructure regarding each methodological question. We decided to omit the issue of statistical requirements. Instead, future studies using the SCED infrastructure should discuss statistical requirements for the respective research question and analysis in a separate pre-registration in the Open Science Framework (https://osf.io/yex48/).

We propose to collect ESM data on 14 consecutive days during each SCED phase. We decided to not limit the study duration during the intervention phase with the aim to gather information about the extent that the daily surveys are used during treatment. Alternatively, a second (or more) 14-day assessment periods could be prompted during treatment (phase C’ or C’’ etc.). We suggest to collect one signal-contingent survey per day with the option of additional event-contingent surveys whenever the patient feels something important had happened. Each event-contingent survey will trigger a measurement burst with additional five surveys, randomly presented within the following hour. This measurement burst enables to monitor momentary mood on a microlevel. We decided to apply a semi-random sampling scheme with random beeps during an individualized time in the evening (e.g., 18-22 h). As delay allowed to respond, we suggest 60 min for the signal-contingent survey with a reminder after 30 min. For the event-contingent survey, we decided to close the survey after 30 min.

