Penetration	Penetration refers to the integration of a practice within a setting	Number of patients and psychotherapists who actually use the SCED infrastructure (e.g., in terms of responding to the ESM surveys; retrieving and discussing the dashboard during treatment or supervision)	(5) ESM data (including signal- and event-contingent surveys of completed ESM surveys (i.e., the last question has been answered)) is used to derive an estimate for the penetration: • Exploration of arithmetic values (e.g., median, range, mean standard deviation) for the number of completed ESM surveys for each SCED phase, especially for the open-ended intervention phase • RoBiNT scale requires each phase to consist of at least five, but not less than three data points for the analysis of SCED data (Tate et al., 2013). We will evaluate each phase separately, with ≥ 5 data points as an acceptable criterion. For each phase, we divide the number of patients who fulfill the acceptable (≥ 5 data points) criterion by the number of participating patients (6) Indication how often patients and psychotherapists retrieved the dashboards either to prepare for treatment or discuss the dashboard during treatment on a 5-point Likert scale (1 = never to 5 = every session) after each SCED phase. Psychotherapists will also be asked to indicate how often they discussed the dashboard with their supervisors • *‘How often did you retrieve the dashboard (e.g., to prepare for treatment or discuss the dashboard during treatment)?’* • *‘How often did you discuss the dashboard together with your supervisor?’*	(5) A rate ≥ 75 is considered substantial use (6) Mean scores of > 3.5/5 on each item are considered substantial use
Implementation costs	All costs needed for an implementation effort	All monetary resources needed for the implementation of the SCED infrastructure. These costs could either be anticipated (e.g., for the m-path software) or unexpected (i.e., they only become clear in the course of implementation)	Implementation costs are also difficult to calculate because they vary substantially in the different settings (7) A list of the costs we have incurred (e.g., required working time of an employee to coordinate the single-case clinic)	

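### Penetration measure (5) lets the survey burst after a single event satisfy the five-data-point criterion for a whole phase

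*Protocol article*

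**What the plan says.** All references are to the protocol article.

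- **What is counted.** Table 3 (Study 5), penetration row, measure (5): "ESM data (including signal- and event-contingent surveys of completed ESM surveys (i.e., the last question has been answered)) is used to derive an estimate" of penetration.
- **The threshold and its reason.** "RoBiNT scale requires each phase to consist of at least five, but not less than three data points for the analysis of SCED data". The plan adopts the upper of these two figures: "We will evaluate each phase separately, with ≥ 5 data points as an acceptable criterion".
- **The rate.** "For each phase, we divide the number of patients who fulfill the acceptable (≥ 5 data points) criterion by the number of participating patients". The success criterion is "A rate ≥ 75 is considered substantial use"; no unit is printed, and it is read here as a percentage.
- **The sampling scheme.** The ESM Protocol section (Study 2) proposes one signal-contingent survey a day for 14 days per phase, with optional event-contingent surveys started by the patient. "Each event-contingent survey will trigger a measurement burst with additional five surveys, randomly presented within the following hour". The stated purpose is different from sampling the phase: "This measurement burst enables to monitor momentary mood on a microlevel".
- **The neighbouring measures.** In the last row of Table 3, compliance (8) and retention (9) use signal-contingent surveys only. Retention also has a threshold of five surveys.
- **The intervention phase.** Table 1, item 3, sets no fixed length: "Intervention phase: open end".

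**The concern.** The five-point minimum is there to ensure that a phase holds enough repeated observations to be analysed as part of a single-case design. A burst supplies up to six observations in about an hour, all following one event that the patient chose to report. Counted singly, they can meet the minimum without giving any information about the rest of a 14-day phase. Table 3 then has two thresholds of five that mean different things: in measure (9), five daily prompts answered; in measure (5), possibly one hour of one day.

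What is at stake is a predefined success criterion. The Study 5 text says that if the criteria are not met, the team will propose another implementation strategy. An overstated penetration rate could remove that prompt for this domain. The Discussion names poor penetration as a risk and says that no stopping rule was set, so the measure should be able to show it.

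**Working it through.** The document gives no figure to reproduce for this measure, so the check is a direct count followed by an illustration.

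**1. Direct count.** One event survey + five burst surveys = 6, and 6 ≥ 5. The event survey plus any four of the five burst surveys is enough. The patient needs 0 of the 14 daily surveys. Without a burst, five daily surveys would be five separate days, 5/14 = 36% of the phase.

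**2. The same patient across Table 3** (one complete burst, no daily surveys in a 14-day phase):

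| Measure | Surveys counted | Result |
|---|---|---|
| (5) Penetration, this phase | signal- and event-contingent | 6 ≥ 5, met |
| (8) Compliance, this phase | signal-contingent | 0/14 = 0% |
| (9) Retention | at least five signal-contingent | nothing contributed; could fail |

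The table does not say whether (9) is judged per phase or over all phases, hence *could*.

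**3. How hard it is to pass on a burst alone.** Let q be the chance that each burst survey is completed (assumed), given a completed event survey. Then P(at least 4 of 5) = 5q⁴(1−q) + q⁵:
- q = 0.7: 0.360 + 0.168 = 0.53
- q = 0.8: 0.410 + 0.328 = 0.74
- q = 0.9: 0.328 + 0.590 = 0.92

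**4. Effect for one patient in a 14-day phase.** Let p be the chance that each daily survey is completed (assumed), X ~ Binomial(14, p), and B ~ Binomial(5, q), with responses independent.
- Daily surveys only: P(X ≥ 5).
- Current wording, one event with its event survey completed: P(1 + B + X ≥ 5).
- Event and burst counted as one point: P(X ≥ 4).
- Five distinct days, with the event day certain to count: P(Binomial(13, p) ≥ 4).

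| p | Daily only | Current, one event (q = 0.5 to 0.8) | Burst as one point | Five distinct days |
|---|---|---|---|---|
| 0.1 | 0.009 | 0.58 to 0.92 | 0.04 | 0.03 |
| 0.2 | 0.130 | 0.83 to 0.98 | 0.30 | 0.25 |
| 0.3 | 0.416 | 0.95 to 0.99 | 0.64 | 0.58 |
| 0.5 | 0.910 | above 0.99 | 0.97 | 0.95 |
| 0.7 | 0.998 | above 0.99 | above 0.99 | above 0.99 |

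**5. Effect on the group rate.** If a share e of patients report one event in the phase, rate = e × P(pass with event) + (1 − e) × P(X ≥ 5). With p = 0.2, q = 0.8 and e = 0.75:
- Current wording: 0.75 × 0.978 + 0.25 × 0.130 = 0.766, above 75%.
- Burst as one point: 0.75 × 0.302 + 0.25 × 0.130 = 0.259.
- No events: 0.130.

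With e = 0.25 or 0.5 the current-wording rate is 0.34 or 0.55, below the criterion. With p = 0.5 the rate is already 0.91 without any events.

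**The case against.** **The table does not mention bursts.** This is true. That burst surveys count is an inference. It is the natural one, because the ESM Protocol section defines only two survey types and attaches the burst to the event-contingent one, and nothing excludes burst surveys, collapses them or asks for different days. If exclusion was intended, one clause would settle it.

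**Penetration is about use, and analysability is measured elsewhere.** Starting an event survey is genuine use, and measures (8) and (9) would expose a patient who answers no daily prompts. This stands in part. It is a reason not to restrict measure (5) to signal-contingent surveys, which would discard real use and nearly duplicate (9). It does not rescue the threshold, which the table itself justifies by the data needed for single-case analysis.

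**The impact is speculative and little depends on it.** Passing on a burst alone takes at least four of five prompts answered within an hour. Measure (5) is one of several pilot criteria, the pilot is to be repeated for another year whatever the result, and the ESM protocol is still to be finalised in Study 2. All of this limits the weight of the point. It does not make the count right, and settling it before Study 5 starts costs little.

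**A stronger reading for the intervention phase.** A reader might infer that five surveys in an open-ended phase is a vanishing share of prompts and that the minimum must be scaled to phase length. The document does not support this. It gives numbers of sessions but no session frequency, so phase length in days is unknown. Therapists may start new intervention phases, and 14-day periods within treatment are an alternative. The RoBiNT minimum is quoted as a count and not a proportion. Measure (5) also already plans median, range, mean and standard deviation of completed surveys per phase, with emphasis on this one. At most, a fixed count of five is a weak marker of use there and should be read beside those descriptive figures.

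**Conclusion.** The point holds for the 14-day phases. As written, and on the natural reading that burst surveys count, one event with at least five of its six surveys completed meets the five-data-point criterion for a patient's phase with no daily survey answered. That follows from the document's own numbers.

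The size of the overstatement cannot be derived from the document. Under the assumed rates it runs from nothing of consequence, where daily completion is 50% or more, to a change of conclusion (13% to about 77%) at 20% daily completion, 80% burst completion and three quarters of patients reporting an event. These figures assume independent responses and the same completion probability for every patient; they illustrate and do not predict.

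Two further inferences should not be drawn. One event does not by itself produce a finding of substantial use, because the rate must still reach 75 across participating patients. Nor does the document show that the effect falls mainly on patients who ignore the daily survey, since it gives no joint data on event and daily responding.

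**What to change.** In Table 3, measure (5), keep the five-point criterion but define a data point in one of two ways:

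1. each event-contingent survey together with its burst counts as one data point; or
2. completed surveys, of either type, are required on at least five distinct days of the phase.

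The second is stricter, because several events on one day count once. Either keeps event-based use in the measure. Report the numbers of event-contingent and burst surveys separately, as descriptive use, beside the per-phase summaries already planned. For the open-ended intervention phase, add a note that the five-point rate is to be read with those summaries.

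The cost is a rewording of one table row before Study 5 begins. No new data are needed. The penetration rate may be somewhat lower than under the current wording.

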Compliance and Retention Rates	Compliance refers to the ratio of completed surveys over the theoretical maximum number of surveys Retention refers to the proportion of participants included in the final analyses	Compliance and retention rates to the ESM surveys intend to evaluate to what extent the data generated in a routine clinical setting could be used for future data analyses to address overarching research questions	(8) Ratio of completed signal-contingent surveys divided by the number of theoretically possible surveys (as an indicator for compliance) (9) Proportion of participants who responded to at least five of the signal-contingent surveys after data cleaning (as an indicator for retention)	(7) Rates of 70–80% are considered satisfactory compliance (8) Rates of 90% are considered satisfactory retention

Note. Definitions are derived by Proctor et al. (2011). Implementation outcome measures will be administered to both patients and psychotherapists after each SCED phase; only the Evidence-based Practice Attitudes Scale (EBPAS) will be administered once at the study beginning (i.e., when patients and psychotherapists decide whether to use the SCED infrastructure); this will allow to compare individuals who are willing to use the SCED infrastructure with those who are not. Criteria for a successful implementation were chosen according to previous research (Schleider et al., 2020); criteria for compliance and retention rates were formulated based on systematic reviews (Rintala et al., 2019; Vachon et al., 2019; Wrzus & Neubauer, 2023); it should be noted, however, that these values were estimated in the context of research studies (as opposed to a routine clinical care setting)

To evaluate our implementation process, we assess several perceptual and behavioral outcome domains (Proctor et al., 2011). We hope to obtain some outcome measures from people who are willing to use the SCED infrastructure, as well as those who are not interested. This will allow us to conduct some exploratory analyzes about how these groups differ. For patients, we expect to collect a relatively diverse sample which will probably allow such a comparison.

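### Penetration measure (5) in Study 5 lets one event and its one-hour survey burst satisfy the five-data-point rule for a whole phase, so the rate can overstate use among low responders

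*Protocol article*

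**What the plan says.** Three elements of measure (5) in Table 3 (Study 5, Penetration) matter here.

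- **What is counted:** completed surveys of both types, "ESM data (including signal- and event-contingent surveys of completed ESM surveys".
- **The threshold and its reason:** "RoBiNT scale requires each phase to consist of at least five, but not less than three data points for the analysis of SCED data", followed by "We will evaluate each phase separately, with ≥ 5 data points as an acceptable criterion".
- **The rate and its cut-off:** for each phase, "we divide the number of patients who fulfill the acceptable (≥ 5 data points) criterion by the number of participating patients", judged by "5) A rate ≥ 75 is considered substantial use". The cut-off is printed without a unit; I read it as per cent.

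The ESM Protocol section (Study 2) sets the sampling: "one signal-contingent survey per day with the option of additional event-contingent surveys whenever the patient feels something important had happened". It then adds: "Each event-contingent survey will trigger a measurement burst with additional five surveys, randomly presented within the following hour". Each fixed phase runs for 14 consecutive days, so it holds 14 evening surveys. The intervention phase is open-ended.

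Retention, measure (9) of the same table, uses the same number five but a narrower count: "Proportion of participants who responded to at least five of the signal-contingent surveys after data cleaning". Compliance, measure (8), is also limited to signal-contingent surveys.

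**The concern.** A minimum number of data points per phase is there to secure repeated observation of that phase. Under this sampling scheme the evening surveys do so automatically, since at one per day five points need five days. Event surveys do not. They are started by the patient, no cap or spacing is stated, and each brings a cluster of five more within the hour. A patient who ignores every evening prompt but answers one burst would be counted as meeting the phase minimum, on readings from a single episode chosen by that patient.

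At stake is a predefined success criterion. The Study 5 text says that if the predefined criteria are missed, the research team will propose another implementation strategy. A rate lifted by bursts could make that need less visible. The patients affected are those with low evening response, whom a penetration measure should pick out.

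**Working it through.** **Inputs from the article:** one evening survey per day; 14 days per fixed phase; five burst surveys per event survey; threshold of five data points; cut-off 75. There is no sample size or error rate to reproduce for this measure, so the check is a count followed by illustrations.

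**Step 1, the count.** One event offers 1 + 5 = 6 surveys, and 6 ≥ 5. The event survey plus any four of its five burst surveys gives 1 + 4 = 5, which meets the rule with no evening survey. If burst prompts fall uniformly over 60 minutes, the fourth is expected at 60 × 4/6 = 40 minutes. If the 30-minute closing time for event surveys also applies to burst surveys, the last reply comes at most about 60 + 30 = 90 minutes after the event survey. On evening surveys alone, five points take at least five days.

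**Step 2, chance of reaching five on evening surveys alone.** Let X be binomial with n = 14 and an assumed response probability p, independent across days.

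| p | P(X ≥ 5) |
|---|---|
| 0.20 | 0.130 |
| 0.25 | 0.258 |
| 0.50 | 0.910 |
| 0.70 | 0.998 |
| 0.80 | 1.000 |

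The burst matters at the top of the table and hardly at all in the two bottom rows, which span the 70–80% that Table 3 calls satisfactory compliance.

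**Step 3, chance that a burst qualifies.** Given a completed event survey and an assumed response probability c to each burst survey, P(at least 4 of 5) = 5c⁴(1 − c) + c⁵. This is 0.19 at c = 0.5, 0.53 at 0.7, 0.74 at 0.8 and 0.92 at 0.9.

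**Step 4, effect on the rate (assumed patient mixes).** Let q be the share of low responders with one qualifying burst in the phase.

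- Half of patients at p = 0.80, half at 0.20: evening-only rate = 0.5 × 1.000 + 0.5 × 0.130 = 56.5%. The rate as written reaches 75% when 0.565 + 0.5 × 0.870 × q = 0.75, so q = 0.185/0.435 ≈ 0.43.
- 60% at 0.80, 40% at 0.25: evening-only rate = 0.6 × 1.000 + 0.4 × 0.258 = 70.3%. It reaches 75% when 0.703 + 0.4 × 0.742 × q = 0.75, so q ≈ 0.16.

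**Step 5, the same mixes counted by distinct days.** A burst now adds at most one day. A low responder with one event day needs four more days from the other 13: P(Bin(13, 0.20) ≥ 4) = 0.253, and P(Bin(13, 0.25) ≥ 4) = 0.416.

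- First mix, q = 0.43: 0.565 + 0.5 × 0.43 × (0.253 − 0.130) ≈ 59%.
- Second mix, q = 0.16: 0.703 + 0.4 × 0.16 × (0.416 − 0.258) ≈ 71%.

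The day count still credits event use, but a single burst no longer carries the rate across 75.

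**The case against.** **Event surveys are use.** Table 3 operationalises penetration as actual use, and event surveys are a function on offer. Measures (8) and (9) serve a different stated purpose, namely whether the data could support later analyses. A reader might infer that the table contradicts itself because (5) has a wider numerator than (8) and (9). That does not follow, since different constructs may have different numerators. This objection stands, and it is why the remedy should not strip event surveys out of (5). It does not rescue the threshold, which the table justifies by analysability and not by use.

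**Measure (9) is a guard.** A patient with one burst and no evening survey fails (9) and scores zero on (8), so a gap would show. This stands in part, but (9) is not stated per phase, whereas (5) is.

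**Bursts are not named in (5).** Correct: counting each burst survey as a data point is the plain reading, not an explicit statement. Nothing excludes them, however. Even without bursts, five self-started event surveys on one day would pass.

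**The burst is a proposal.** The ESM Protocol is to be finalised in Study 2 and tested in Study 4, so the burst may change before Study 5. Measure (5) is nonetheless written alongside the present scheme.

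**The consequences are limited.** A reader might infer that burst surveys dominate the descriptive counts, or that phases passed this way could not support a phase comparison. The article supports neither. Even two assumed events give 12 of 14 + 12 = 26 possible points (46%). Routine care relies on visual inspection, and statistical requirements are left to separately registered studies. The pilot is also repeated for another year whatever the result.

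**Conclusion.** The point holds as a weakness in how the criterion is defined. On the article's own figures, one event survey and four burst replies satisfy the five-point rule for a whole phase, and no provision requires separate days, caps events or excludes bursts. The rate compared with 75 can therefore overstate use among low responders.

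The size cannot be stated, because event frequency and burst response are not given. In the assumed mixes above, 43% or 16% of low responders with one qualifying burst would move the rate from 56.5% or 70.3% to 75%. With evening response near 70–80%, the effect is negligible. The figures rest on independence between days and on burst surveys counting as data points. A reader might go further and infer that the pilot will wrongly declare substantial use; the documents show only that it could.

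Severity is moderate to minor. This is one descriptive success criterion in a pilot, attached to a sampling scheme that is not yet final.

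**What to change.** In Table 3, measure (5), define five or more data points as at least five distinct days in the phase with at least one completed survey, signal- or event-contingent. A burst then counts once at most per day, and event use is still credited. In the descriptive part of (5), report signal, event and burst counts separately for each phase. Optionally, show the signal-only rate per phase beside it for comparison with measure (9).

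Restricting (5) to signal-contingent surveys would also remove the inflation, but it would make (5) almost a per-phase copy of (9) and drop event use from a measure of use.

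The cost is one line in the table and the matching line of analysis code. No data are lost and no new data are needed. The penetration rate may come out slightly less favourable.
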